### 2.5 Randomization and blinding

Following baseline assessments, participants will be split into two groups: an experimental group and a control group. The randomization plan, including allocation groups and follow-up measurements (as shown in Figure 1), will be generated using online software that employs a random block sizes method. This randomization method guarantees an allocation concealment format, meaning that the person responsible for the task will be unaware of the next group allocation. Due to the protocol differences, it is not feasible to blind the participants or treating clinicians to the condition. Nonetheless, the research team member performing data collection and analysis will be blinded to the group allocation, whether control or experimental.

**FIGURE 1 F1:**
[figure not shown]
Flowchart describing the search strategy.

### 2.6 Intervention

The control group will receive standard dysphagia care, while the intervention group will receive both standard and kinesiology tape applications.

Routine dysphagia care consists of oral exercises (e.g., repeated dry swallowing five consecutive times, followed by a 10-s rest period. This sequence will be repeated a total of 10 times), compensatory techniques (e.g., chin tuck, head rotation, and head tilt), swallowing therapeutic maneuvers (e.g., supraglottic swallowing, super-supraglottic swallow, effortful swallowing, and the Mendelsohn maneuver), and other exercises used to improve swallowing physiology (e.g., the Shaker exercise and Masako maneuver).

This routine will be implemented 4 days a week, with one daily session. Sessions will last approximately 30 min, resulting in 15 sessions.

Sessions will be led by a team of two senior nurses specialized in rehabilitation, experts in dysphagia care, and trained in kinesiology taping application, with more than 10 years of clinical experience.

A 5 cm wide, 0.5 mm thick kinesiology tape will be applied as follows: Participants will sit upright in a chair with their head and neck in a neutral position. The anterior neck will be cleaned with an alcohol swab for optimal tape adhesion. The application will follow the method outlined by Park et al. (25) (Figure 2).

**FIGURE 2 F2:**
[figure not shown]
Application of kinesiology taping.

Team members will customize an I-shaped tape and a reverse V-shaped tape. The hyoid bone and thyroid cartilage will be marked with a pen. First, an I-shaped tape will be applied by pulling it downward to the level of the thyroid notch to wrap around the thyroid cartilage and attach it to the sternum. Second, the team members will attach a reverse V-shaped tape from the hyoid bone to the superior medial surface of the clavicle on both sides. Finally, they will cover the hyolaryngeal complex horizontally to restrict its movement throughout swallowing, ensuring the tape is securely attached.

Tapes will be replaced daily with an application at approximately 70%–80% tension.

### 2.7 Concomitant treatments and medication

Participants can continue their routine medications for underlying diseases such as hypertension and diabetes. However, the use of additional benzodiazepines, antipsychotics, and anti-epileptics that may impact their swallowing function is permitted only if deemed necessary. If a participant takes medication that could affect their swallowing ability, it will be documented in the case report form.

### 2.8 Data collection

We will use the participants’ clinical records to collect the following characteristics: Participants’ sex, age, educational level, occupation, brain tumor history, and comorbidities.

A blinded researcher will assess primary study outcomes at baseline *T0* and after intervention *T1* (until 24 h after the final session).

The following domains will assess the primary outcomes of this study:

The Fiberoptic Endoscopic Evaluation of Swallowing (FEES) will be used alongside the Penetration-Aspiration Scale (PAS). Participants will be asked to swallow solid, semi-liquid, and liquid food. The assessment will be stopped if aspiration occurs, defined as the entry of food into the airway below the true vocal cords (26). The PAS is an 8-point scale that evaluates the severity of food or liquid entering the airway during swallowing, based on FEES observations. It assesses how far the material penetrates and whether it is cleared. Scores range from no airway entry to material entering below the vocal cords, not being cleared, and no protective response (silent aspiration).Gugging Swallowing Test (GUSS). The GUSS is a clinical tool used to assess the safety of swallowing in patients and identify the risk of aspiration. The test evaluates the patient’s ability to swallow different food and liquid consistencies, beginning with thickened fluids and gradually progressing to thin liquids. The GUSS is divided into two main parts: the indirect swallowing test, which assesses the patient’s ability to swallow saliva and checks for symptoms of dysphagia, such as coughing or drooling, and the direct swallowing test, which observes for signs of aspiration or choking as the patient is given substances of increasing difficulty (semisolid, liquid, and solid).

The maximum score indicates safe swallowing without aspiration risk, while lower scores suggest higher aspiration risk.

Dysphagia Handicap Index (DHI). The DHI is a self-reported questionnaire designed to assess the impact of dysphagia swallowing on an individual’s daily life. It evaluates three key dimensions: physical, functional, and emotional aspects of living with dysphagia. The DHI consists of 25 items, scored using a Likert scale, with higher scores indicating a more significant perceived handicap.Functional Oral Intake Scale (FOIS). The FOIS is a clinical tool used to evaluate a patient’s ability to consume oral foods and liquids. It provides a standardized measure of functional oral intake, particularly in individuals with dysphagia. The scale consists of 7 levels, ranging from complete reliance on non-oral feeding to the ability to eat and drink without restrictions.

The secondary outcome of this study will be evaluated at T1 by the following key domains:

(1)   Recruitment (number of patients that express interest in participating);(2)   Enrollment (number of patients that participate in the program);(3)   Retention (number of sessions and percentage of enrolled participants who completed final program assessments);(4)   Satisfaction (assessed with an exit survey) will be recorded using binary response questions (yes/no) and a 5-point Likert-type scale;(5)   Adverse events that happen throughout the intervention (will be documented in the case report form).

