## Abstract

Dysphagia is a common complication in brain tumor survivors, either as a direct symptom of the tumor or a result of neurosurgery. With improved survival rates, the need for effective rehabilitation strategies is more crucial than ever. Kinesiology taping has shown promise in dysphagia rehabilitation for stroke patients, but its potential in brain tumor survivors is largely unstudied and represents a significant research opportunity. This pilot study aims to assess feasibility and gather preliminary data on the impact of kinesiology taping, in addition to standard dysphagia care, on improving swallowing function in brain tumor survivors post-neurosurgery. This 1:1 parallel-group randomized controlled trial will recruit 62 brain tumor survivors with oropharyngeal dysphagia from a Neurosurgery Inpatient Unit in Portugal. Participants will be randomized into two groups: the control group, receiving standard dysphagia care, and the experimental group, receiving kinesiology taping applied to the suprahyoid muscles in addition to standard care. The intervention will last 15 sessions over 4 weeks. Primary outcomes will be assessed using the FEES Penetration-Aspiration Scale, Gugging Swallowing Test (GUSS), Dysphagia Handicap Index (DHI), and Functional Oral Intake Scale (FOIS). This study will evaluate the efficacy of kinesiology taping as a supplementary therapy for dysphagia rehabilitation in brain tumor survivors. The potential improvements in clinical care and patient outcomes are significant, reinforcing the importance of this research in enhancing the quality of life for these survivors.

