### 3.1 Strengths and limitations

Although this randomized controlled trial is the pioneer in exploring the effectiveness of kinesiology taping for treating dysphagia in survivors of brain tumors after undergoing neurosurgical intervention, we have built the protocol based on previous work examining the effectiveness of kinesiology taping on stroke survivors, thus expecting to achieve positive outcomes. In addition, the chosen outcome measures represent those most practically implemented in the clinical settings.

To ensure this randomized controlled trial was designed following trial standards, we used the SPIRIT statement, which is widely endorsed as an international standard for trial protocols, to enhance the quality, transparency, and completeness of trial protocols, which can help to improve the overall reliability and validity of this clinical trial results. Nonetheless, it should be noted that this trial has limitations. First, blinding is essential to minimize bias that can affect study outcomes. In this trial, it is not feasible to blind participants or team members who will implement the intervention. However, to minimize data collection and analysis bias, the research team members responsible for these tasks will be blinded to the treatment allocation, whether the participant received the intervention or the placebo/control. Second, there is no uniform standard care treatment for people with dysphagia in Portugal. For this reason, team members will perform the usual treatment in the Neurosurgery Inpatient Unit, bearing in mind that the time and periodicity of the intervention applied in this trial are possibly more prolonged than the time of rehabilitation care practiced in other similar units. Third, we expect some participants to not complete the intervention due to being transferred to other units or facilities (e.g., rehabilitation units). To minimize the impact of this occurrence on the research results, we assume a dropout rate of 15% when calculating the study’s sample size.

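### The stated blinded assessment of the primary outcomes does not hold for the DHI, which unblinded participants rate themselves against a no-tape control

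*Protocol article*

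**What the plan says.** The abstract and section 2.8 name four primary outcomes: FEES with the Penetration-Aspiration Scale (PAS), GUSS, DHI and FOIS. They are not ranked.

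On who assesses them, section 2.8 says: "A blinded researcher will assess primary study outcomes at baseline", and again after the intervention. No outcome is excepted. The same section says of the DHI: "The DHI is a self-reported questionnaire designed to assess the impact of dysphagia swallowing". It adds that higher scores mean a greater perceived handicap.

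On blinding, section 2.5 says that "it is not feasible to blind the participants or treating clinicians to the condition", and that "the research team member performing data collection and analysis will be blinded to the group allocation, whether control or experimental".

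On the comparator, section 2.6 says: "The control group will receive standard dysphagia care, while the intervention group will receive both standard and kinesiology tape applications". No sham tape is described.

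Section 3.1 gives the lack of participant blinding as the first limitation. Its response is that "to minimize data collection and analysis bias, the research team members responsible for these tasks will be blinded to the treatment allocation". The same sentence ends with "whether the participant received the intervention or the placebo/control".

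**The concern.** Blinding the person who collects the data protects an outcome when that person makes the judgement. For a self-completed questionnaire the participant makes it. Here the participant knows whether there is tape on the neck, and the researcher can only hand over, record or total the form. The statement in section 2.8 is therefore not true of one primary outcome in four.

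This affects what the trial can conclude. A between-arm difference in DHI change would combine any effect on swallowing with any effect of knowing the allocation, and the design cannot separate the two. The abstract describes a pilot that gathers preliminary data, but it also says the study will evaluate efficacy. A reader who relies on section 2.8 would give a DHI result the same protection from bias as a PAS result.

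**Working it through.** **Step 1. Who rates each primary outcome, and is that person blinded?**

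| Primary outcome | Who makes the rating (section 2.8) | Blinded under section 2.5? |
|---|---|---|
| FEES-PAS | observer, from endoscopic observation | yes, as planned |
| GUSS | observer, clinical tool | yes, as planned |
| FOIS | observer, clinical tool | yes, as planned |
| DHI | participant, self-report | no |

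The unqualified statement in section 2.8 holds for three rows and fails for the fourth.

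**Step 2. Does the mitigation in section 3.1 reach the fourth row?** It blinds data collectors and analysts. Neither produces the DHI answers, so it does not. No other mitigation is given.

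**Step 3. The plan's own sample size.** Section 2.4 gives f = 0.25, two groups, two measurements, correlation 0.5, non-sphericity correction 1, alpha 0.05, power 80%, and reports 34 per group. For the within-between interaction, lambda = f² × N × m / (1 − rho). With N = 34 in total, lambda = 0.0625 × 34 × 2 / 0.5 = 8.5 on 1 and 32 degrees of freedom, and power is 0.807. These inputs therefore give 34 in total (17 per group), and the stated 34 per group is not reproduced. The dropout step is consistent: 34 / 0.85 = 40 per group, 80 in all. The abstract says 62, which is 31 per group. These are separate matters. Step 4 takes 34 per arm as the plan states it and shows 31 and 40 alongside.

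**Step 4. What a bias of a given size would do.** With two groups and two time points, the group-by-time interaction is equivalent to a two-sample t-test on change. Assumptions: true effect zero, and a shift of b SD of DHI change between arms that comes from knowledge of allocation alone. The documents give no value for b.

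Noncentrality = b × √(n/2), with 2n − 2 degrees of freedom, two-sided alpha 0.05. For n = 34, √17 = 4.123, so b = 0.2, 0.3 and 0.4 give noncentralities of 0.82, 1.24 and 1.65.

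| Assumed b (SD of change) | 31 per arm | 34 per arm | 40 per arm |
|---|---|---|---|
| 0.1 | 0.067 | 0.069 | 0.073 |
| 0.2 | 0.121 | 0.128 | 0.143 |
| 0.3 | 0.213 | 0.230 | 0.263 |
| 0.4 | 0.341 | 0.369 | 0.424 |
| 0.5 | 0.491 | 0.529 | 0.598 |

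Each entry is the probability of two-sided p<0.05 with no true effect. All exceed 0.05, and for a given b the probability rises with n, so a larger sample does not cure the problem. The formula is symmetric in b: a shift against tape would give the same rejection rate in the other direction, and could hide a real benefit.

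**The case against.** The strongest reply is that the limitation is already disclosed. Section 2.5 says plainly that participants are not blinded, and section 3.1 lists this first among the limitations. Read with section 2.5, the blinded researcher in section 2.8 may simply be the person who administers and records the form, which would make the sentence loose rather than false. Section 3.1 claims only to reduce bias in collection and analysis and does not say that expectation is controlled. All of this stands: nothing is concealed. What remains is that section 2.8 does not separate observer-rated from self-rated outcomes, and that the consequence for the DHI is stated nowhere.

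A second reply is that a patient-reported outcome is a defensible choice in a trial that cannot be blinded, because perceived handicap is not what the three clinical scales measure. That also stands. A reader might infer that the DHI has to be removed from the primary outcomes, but the documents do not support so much. Demotion is one option among several.

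A third reply concerns size and direction. The 0.2 to 0.4 SD range has no anchor in the documents. Nor is a bias in favour of tape established: section 2.6 describes tape replaced daily and meant to restrict movement in swallowing, and that burden could raise perceived handicap in the taped arm. The percentages describe the assumption and are not an estimate for this trial.

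Two further inferences should be resisted. A reader might infer that a DHI result alone would be enough to claim efficacy. The article states no success rule across the four outcomes, and one may sit in an analysis plan that is not shown. A reader might also infer from the placebo wording in section 3.1 that a sham was intended or is being claimed. Sections 2.5 and 2.6 leave no doubt that the comparator is standard care, so the wording is a slip.

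**Conclusion.** The point holds in a limited form. The blinded assessment that section 2.8 states for the primary outcomes does not apply to the DHI, one of four unranked primary outcomes, and the mitigation in section 3.1 does not address it. This rests on the text alone and on no assumed figure.

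The size of the consequence does rest on an assumption. If knowledge of allocation shifted DHI change in favour of tape by 0.2 to 0.4 SD, the chance of p<0.05 with no true effect would be about 13% to 37% at 34 per arm. The true size and direction are unknown. The point does not extend to FEES-PAS, GUSS or FOIS, which a blinded rater can protect.

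**What to change.** In section 2.8, limit the blinded-assessment statement to the observer-rated outcomes (FEES-PAS, GUSS and FOIS), and say that the DHI is rated by participants who know their allocation.

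In the same section, state that a DHI difference without support from the blinded observer-rated outcomes will not be read as evidence of efficacy. Listing the DHI as a secondary patient-reported outcome, in section 2.8 and the abstract, is one way to do this. Keeping it primary with that rule stated is another.

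In section 3.1, replace the placebo/control label with no-tape control, and add that blinded data collection does not protect the DHI.

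Cost: the same data are collected and no participant burden is added. The DHI carries less weight in the efficacy conclusion. Because the trial is registered and subject to ethics evaluation, those documents may need a matching update, particularly if the status of the DHI changes.

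### Satisfaction is surveyed only at T1, so early leavers have no survey point and acceptability can be overstated; the retention denominator can also be read to omit randomised patients who never start

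*Protocol article*

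**What the plan says.** Section 2.8 lists five secondary domains: recruitment, enrolment, retention, satisfaction and adverse events. Their timing is set by one sentence: "The secondary outcome of this study will be evaluated at T1 by the following key domains". The same section places the follow-up assessment "after intervention *T1* (until 24 h after the final session").

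Three of the definitions matter here:

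- "Satisfaction (assessed with an exit survey) will be recorded using binary response questions (yes/no) and a 5-point Likert-type scale".
- "Enrollment (number of patients that participate in the program").
- "Retention (number of sessions and percentage of enrolled participants who completed final program assessments").

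The protocol also describes how patients may leave before T1. Section 2.3 removes anyone who develops pneumonia or becomes medically unstable. Section 2.10 allows consent to be withdrawn at any time. Section 3.1 states that "we expect some participants to not complete the intervention due to being transferred to other units or facilities". Section 2.5 places randomisation after baseline assessment, so a patient can be randomised without yet having attended a session.

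**The concern.** The abstract names feasibility as an aim of the pilot, and these five domains are the outcomes that address it. Acceptability of the tape is a central part of that aim.

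A survey fixed at the end of the programme is answered by those who got there. Patients who leave early are the ones whose view of the tape is most likely to differ. Some may leave because of the tape itself, which could happen in one arm only. If they are not asked, the satisfaction figure describes completers but may be read as describing everyone offered the treatment.

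The retention definition raises a related but smaller question. If enrolment means having taken part in sessions, a patient randomised and then lost before the first session is in neither the numerator nor the denominator. That reading can only raise the retention percentage. A later trial planned on either figure could underestimate its losses or overestimate how well the tape is accepted.

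**Working it through.** **The plan's own figure.** Section 2.4 gives 34 per group and 15% dropout. 34 / (1 − 0.15) = 40 per group, or 80 in total, so the stated inflation reproduces. The expected losses are 0.15 × 80 = 12, which leaves 68 reaching T1.

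**Satisfaction.** The protocol gives no satisfaction rates, so those below are assumptions. Let d be the proportion not completing, s_c the proportion satisfied among completers and s_n the proportion satisfied among leavers.

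- Reported at T1: s_c
- Over all randomised: (1 − d) × s_c + d × s_n
- Overstatement: d × (s_c − s_n)

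With d = 0.15 (section 2.4) and s_c = 0.90 (assumed):

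| s_n (assumed) | Over all randomised | Reported | Overstatement |
|---|---|---|---|
| 0.90 | 0.765 + 0.135 = 90% | 90% | 0 points |
| 0.50 | 0.765 + 0.075 = 84% | 90% | 6 points |
| 0 | 0.765 + 0 = 76.5% | 90% | 13.5 points |

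If non-completion were 25% (assumed) and s_n = 0.50, the figure over all randomised would be 0.675 + 0.125 = 80% against 90% reported.

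**Retention.** The number of losses before the first session, k, is not given and is also an assumption. Over all randomised, retention is 68/80 = 85.0%. If never-starters are left out of the denominator, it is 68 / (80 − k):

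| k of the 12 losses | Calculation | Retention |
|---|---|---|
| 0 | 68/80 | 85.0% |
| 2 | 68/78 | 87.2% |
| 4 | 68/76 | 89.5% |
| 6 | 68/74 | 91.9% |

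The abstract gives 62 patients rather than 80. On that total, 15% is about 9 losses and 53 complete. Retention is 53/62 = 85.5% over all randomised and 53/58 = 91.4% if 4 never start. The choice of total does not change the picture.

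**The case against.** **Timing.** Being evaluated at T1 need not mean being collected only at T1. The same lead-in sentence covers recruitment and adverse events, which cannot arise only on the last day, so it may mean tallied by T1. An exit survey could also be given whenever a patient exits. This stands as a possible reading, and it makes completers-only an inference. But no survey at early exit is described, and the T1 timing points the other way.

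**Direction.** The losses the protocol names are mainly transfer and medical instability, not dislike of the tape. Section 2.3 also screens out patients with skin disorders or tape allergy and requires the ability to swallow against the tape. This stands too: inflation is possible, not certain, and the zero-bias row in the table is a real case.

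**Retention.** Patients who start and then drop out stay in the denominator and count as losses, which is correct. Section 3.1 speaks of not completing the intervention, not of never starting it. Section 2.5 already uses the word participants for those being split into groups, so enrolled may simply mean randomised, and the bias would then vanish. All of this stands. What remains is a loose definition with one favourable reading.

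**Two wider readings that the document does not support.** A reader might infer that all the feasibility outcomes are defined on those who took part. They are not: the first domain is "Recruitment (number of patients that express interest in participating") and the last is "Adverse events that happen throughout the intervention (will be documented in the case report form"), and neither is limited to completers. A reader might also fault recruitment for lacking a count of eligible or approached patients. A condensed article may leave that to the full protocol, so it is not raised here.

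**Conclusion.** The point on satisfaction holds. As written, section 2.8 gives early leavers no survey point, although the protocol expects some patients to leave early. The reported figure can therefore exceed the figure over all randomised by the non-completion proportion times the gap in satisfaction. That is 6 percentage points at 15% non-completion with 90% against 50% satisfied, and zero if leavers are equally satisfied. The satisfaction rates are assumed; only the 15% comes from the protocol.

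The point on retention holds only as an ambiguity to be closed. Under the favourable reading, 85.0% becomes 87.2% or 91.9% if 2 or 6 of 12 losses never start, and it is unchanged if none do. A reader might conclude that retention is shown to be biased, but the text does not compel that reading and gives no number of never-starters.

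The between-group analysis of the primary outcomes is not affected.

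**What to change.** In section 2.8:

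1. Give the existing exit survey at T1 or at the time of stopping or transfer, whichever comes first. Report it by arm, with the number responding out of all randomised, so that patients too unwell or unwilling to answer remain visible.
2. Define enrolment as the number randomised, and retention as the number with T1 completed divided by all randomised, by arm. The number of sessions, already part of the retention definition, can stay alongside it.

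No new instrument or change in sample size is needed. The cost is some rewording, a survey to hand out at early exit, and probably slightly less favourable figures. The change should be made before recruitment starts, because the views of patients who have already left may not be recoverable.
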